## Abstract

**Background:**

Understanding how and why de-implementation of low-value practices is sustained remains unclear. The Paediatric Research in Emergency Departments International CollaboraTive (PREDICT) Bronchiolitis Knowledge Translation (KT) Study was a cluster randomised controlled trial conducted in 26 Australian and New Zealand hospitals (May-November 2017). Results showed targeted, theory-informed interventions (clinical leads, stakeholder meetings, train-the-trainer workshop, targeted educational package, audit/feedback) were effective at reducing use of five low-value practices for bronchiolitis (salbutamol, glucocorticoids, antibiotics, adrenaline and chest x-ray) by 14.1% in acute care settings. The primary aim of this study is to determine the sustainability (continued receipt of benefits) of these outcomes at intervention hospitals two-years after the removal of study supports. Secondary aims are to determine sustainability at one-year after removal of study support at intervention hospitals; improvements one-and-two years at control hospitals; and explore factors that influence sustainability at intervention hospitals and contribute to improvements at control hospitals.

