### Sustainability: definition and overview of research

Sustainability studies are rare, with the few undertaken reporting poor long-term (sustained) compliance [17, 18]. This area of research is complicated by no clear or consistent definition of sustainability [19, 20]. Common elements of sustainability have been identified, namely, continued capacity to deliver the intervention, continued provision of the implementation intervention, and ongoing clinical benefit from the intervention [21]. Additionally, there is debate about distinguishing between *sustainability* and *sustainment* [22]. For our purposes, we define sustainability as the degree to which an evidence-based innovation, after external support has ceased, can deliver its benefits as intended over a prolonged period of time i.e. sustained benefits [17, 23]. We define sustainment as the continued use of an implementation intervention i.e. its sustained use [17, 23].

To date, measurement of the ongoing effect of implementation research largely reports success by the ‘clinical outcomes’ that the intervention was designed to change (i.e. sustainability of improved clinical care) [20]. Often there is insufficient reporting on and evaluation of continuation of the process or implementation of the evidence-based intervention (i.e. sustainment) that was used to bring about the change (i.e. sustainment of education delivery or use of clinical champions etc) [18, 20]. Yet systematic reviews assessing the sustainability of effective behaviour change studies with multiple behaviour change components found 60% maintained implementation of only one component of the proven intervention [19, 24, 25]. Thus the measurement of both sustainability and sustainment are important for the long-term understanding of implementation interventions [26]. For the purpose of this study, we define sustainability as the sustained benefits, i.e. the continued clinician behaviour change (no use of the five low-value bronchiolitis practices) [27]. We define sustainment as the continued use of the targeted theory-informed bronchiolitis implementation strategy [23, 27].

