Findings of the PREDICT Bronchiolitis KT Study demonstrated that, when compared with control hospitals, intervention hospitals significantly improved adherence in management of bronchiolitis during the acute care period (first 24 hours of hospital presentation) for the five key low-value practices as per Australasian Bronchiolitis Guideline recommendations (14.1% adjusted risk difference, 95% CI, 6.5-21.7%; *P* < .001) [4, 34]. Specifically, during the acute care period (first 24 hours of hospital presentation), adherence to the Australasian Bronchiolitis Guideline recommendations with no use of salbutamol, glucocorticoids, antibiotics, adrenaline and CXRs, was 85% (95% CI, 82.6-89.7%) in the intervention group hospitals compared with 73% (95% CI, 65.3-78.8%) in the control group hospitals [4, 34]. At trial completion (November 2018), up to four nurses and doctors from each of the 13 control hospitals attended a 1 day workshop where they were given training and provided with intervention materials (Table 1). However, no on-going facilitation was provided.

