• The difference between control and intervention group hospitals in the proportion of infants presenting to hospitals with bronchiolitis who received care that adhered with each of the five individual Australasian Bronchiolitis Guideline Recommendations known to have no benefit^b^ in the acute care period: a) two- years (2019); following the completion of the PREDICT Bronchiolitis KT Study [4, 34]; and b) one- year (2018); following the completion of the PREDICT Bronchiolitis KT Study [4, 34];	
• The difference between control and intervention group hospitals in the proportion of infants presenting to hospital with bronchiolitis who received care that adhered with all five Australasian Bronchiolitis Guideline Recommendations known to have no benefit^b^ in the acute care period: a) two- years (2019) following the completion of the PREDICT Bronchiolitis KT Study (composite outcomes of all five practices) [4, 34]; and b) one- year (2018) following the completion of the PREDICT Bronchiolitis KT Study (composite of all five practices) [4, 34];	
• The trends in the proportions of infants presenting to hospital with bronchiolitis who received care that adhered with each of the individual five Australasian Bronchiolitis Guideline Recommendations known to have no benefit^b^ yearly from 2014 to 2019 in the acute care period, at control and intervention group hospitals [34].	

^a^ First 24 hours of hospitalisation, ^b^ no use of: i) salbutamol, ii) glucocorticoids, iii) antibiotics, iv) adrenaline, and v) chest x-ray

An a priori definition of sustained improvements will be based on the 7% median improvement achieved in the PREDICT Bronchiolitis KT Study [4]. Practices will be defined as sustained when there is either a maximum of a seven percentage point decrease or any level of improvement (i.e. -7% to infinity) from the participating hospital’s individual post-implementation results based on a composite outcome of the five low-value practices of interest [4, 34].

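### The seven-point tolerance for calling practice sustained equals the median gain it is based on, so a hospital that gained 7 points or less can lose all of its gain and still qualify

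*Protocol article*

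**What the plan says.** The rule stands below Table 3 in the quantitative Data analysis section. Its rationale is that "An a priori definition of sustained improvements will be based on the 7% median improvement achieved in the PREDICT Bronchiolitis KT Study". The operational sentence follows: "Practices will be defined as sustained when there is either a maximum of a seven percentage point decrease or any level of improvement", with the range given as "i.e. -7% to infinity". The reference point is each participating hospital's "individual post-implementation results based on a composite outcome of the five low-value practices of interest", which means its own 2017 composite adherence.

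The Abstract gives the primary aim as to "determine the sustainability (continued receipt of benefits) of these outcomes at intervention hospitals two-years after the removal of study supports". The section on the definition of sustainability says "we define sustainability as the sustained benefits, i.e. the continued clinician behaviour change". The Aim section states that the a priori definition will be used, and the Discussion presents having one as a feature of the study.

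The text shown does not require that any part of a hospital's gain be kept, or that 2019 adherence exceed the pre-trial level.

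**The concern.** A tolerance on loss of benefit is normally a fraction of the benefit, so that passing the test means some benefit remains. Here the tolerance and the gain it comes from are the same number, and the boundary is included. At that boundary a hospital with the median gain has nothing left, yet it is labelled sustained.

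The label is the study's stated criterion for whether the improvement lasted. The interviews then explore factors behind sustainability and non-sustainability. Hospitals back at their starting level but labelled sustained would tilt the main message towards success and could blur that comparison.

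**Working it through.** **Inputs from the protocol.** Median improvement 7%; allowed fall 7 percentage points; reference is each hospital's 2017 composite (all from Data analysis). Parent-trial effect "14.1% adjusted risk difference, 95% CI, 6.5-21.7"; adherence 85% in intervention and 73% in control hospitals (The PREDICT Bronchiolitis KT Study). ICC 0.11, coefficient of variation 0.16, 12 hospitals of 150 infants (Sample size). Parent trial: 3240 infants in 26 hospitals, so 3240/26 ≈ 125 per hospital.

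**Step 1: the other 7% in the plan.** The sample size section gives a confidence-interval half-width of 7%. Design effect = 1 + ((1 + 0.16²) × 150 − 1) × 0.11 = 17.81. Half-width = 1.96 × √(0.85 × 0.15 / 1800 × 17.81) = 0.0696, so the stated 7% reproduces. It describes the precision of a group proportion. It is not the reason given for the margin and does not justify it.

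**Step 2: the margin against its basis.** Allowed loss / median improvement = 7/7 = 100%. The share retained at the boundary is 0% for a hospital with the median gain.

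**Step 3: the rule by size of gain.** A hospital with gain g that reverts fully changes by −g, and passes if g ≤ 7. The smallest share of gain that still passes is 1 − 7/g.

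| 2017 gain (points) | Full reversion passes? | Lowest passing position against the pre-trial level |
|---|---|---|
| 5 | yes | 2 points below |
| 7 | yes | level with it |
| 10 | no | 3 points above (30% kept) |
| 14.1 | no | 7.1 points above (about 50% kept) |
| 20 | no | 13 points above (65% kept) |

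**Step 4: how many hospitals.** If the 7% is the median of hospital-level before-after gains in percentage points, about half of hospitals gained 7 points or less and fall in the rows where full reversion passes. This is conditional, because the text does not say what the median is taken over. Simulating gains spread symmetrically around 7 adds no evidence: a cutoff at the centre of the distribution returns about one half by construction.

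**Step 5: behaviour with sampling error.** Assumptions: true 2017 adherence 85%, 125 or 150 infants in 2017, 150 in 2019, point estimates compared, exact binomial calculation.

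| True loss by 2019 | Called sustained |
|---|---|
| none | about 95% |
| 7 points | about 50% |
| 10 points | about 26% |
| 14.1 points | about 7% |

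The standard error of one hospital's 2017 to 2019 difference, with 85% in both years, is √(0.1275/125 + 0.1275/150) = 0.043, or about 4 points.

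**Step 6: would a smaller margin cure it?** With a margin of 3.5 points (half of 7, for illustration), a true 7-point loss would be called sustained about 23% of the time. A hospital with no true loss would be called sustained only 79 to 81% of the time. A group-level half-width of 3.5 points would need 17.81 × 0.1275 × 1.96² / 0.035² ≈ 7,120 infants, or about 47 hospitals of 150. The planned audit cannot resolve that.

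**The case against.** The strongest defence is that the only composite effect size the protocol reports is the 14.1-point adjusted risk difference. Against that, seven points keeps about half. A group fall from 85% to 78% would still leave 5 of the 12 points separating the arms in 2017. This is a fair reading of the group effect, but the protocol names the 7% median, not 14.1, as the basis, and measures the fall from each hospital's own result.

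A second defence is that the section on definitions first speaks of the degree to which benefits continue, so a tolerance band is a lenient choice and not a logical contradiction. That stands in part: leniency is legitimate, but a tolerance equal to the whole gain leaves nothing to call continued benefit.

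Third, the label is not the only output. The primary outcome is 2019 composite adherence, reported by group with 95% confidence intervals. Table 3 adds between-group differences and yearly trends for each practice. Reversion could therefore be seen, although the formal label would not register it in hospitals with small gains.

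A reader might also infer three stronger points that the documents do not support:

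- **That any hospital losing its whole gain passes.** It does not if the gain exceeded 7 points.
- **That half of all hospitals are affected as a matter of definition.** That depends on an unstated meaning of the 7%.
- **That the rule cannot tell kept benefit from lost benefit.** It does discriminate: about 95% pass with no true loss, against about 50% with a true 7-point loss.

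**Conclusion.** The concern holds for hospitals whose 2017 gain was 7 points or less. They can return to their pre-intervention level, or fall below it when the gain was under 7, and still be labelled sustained. This follows from the protocol's own two figures and does not fit its definition of sustainability as continued benefit. Hospitals that gained more than 7 points must keep part of the gain.

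The share of hospitals affected is about half only on the assumption that the 7% is a median of hospital-level gains in percentage points. The protocol leaves open whether it is taken over hospitals or practices, is absolute or relative, and is before-after or against control. That gap in the basis of the key threshold needs closing in any case.

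**What to change.** 1. State what the 7% is the median of, and what fraction of the gain the seven-point margin is meant to preserve.
2. Add a second condition: 2019 composite adherence must also exceed the hospital's own pre-intervention level. Apply the same check to the intervention group as a whole. Report both with confidence intervals, and name the pre-trial years that form the baseline.
3. Report hospitals with no 2017 gain separately, as having no improvement to sustain.
4. The present seven-point label can be reported alongside.

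Any specific retained fraction, such as half, is for the sponsor to justify. At about 4 points of standard error per hospital difference it is a real trade-off, and simply shrinking the margin would mislabel many hospitals that lost nothing.

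The cost is a change of wording and one further comparison. Table 1 refers to hospital data for 2014 to 2017, and Table 3 plans yearly trends from 2014 to 2019 in both groups, so no new recruitment is needed. Those trends are listed by individual practice, so the pre-trial composite would have to be derived from the same records. The downside is that fewer hospitals will be labelled sustained. Hospital-level labels will also remain noisy with 125 to 150 infants per year, so some hospitals with small gains will still be misclassified.

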#### Qualitative study

##### Recruitment of clinical staff for interviews

The Clinical Director of either the EDs or paediatric inpatient areas of the participating hospital will be approached by email to confirm their hospital’s participation in the qualitative interviews. The Clinical Director (or site Principal Investigator) will be requested to send participant information forms to eligible medical and nursing staff. Phone or email contact with the Clinical Directors or site Principal Investigator will be made by the research team approximately 1 week after sending the recruitment pack to check receipt and facilitate recruitment.

Qualitative group interviews will be undertaken with a purposive sample of nurses and doctors at each hospital who treat infants with bronchiolitis in participating EDs and paediatric inpatient areas. These will be undertaken at intervention and control group hospitals at each site or via telephone/video interviews. Where it is not possible to undertake semi-structured group interviews at the hospital due to logistical issues or COVID-19 restrictions, interviews will be undertaken with individual staff members. To be eligible for interview, participants must be: on an active practice roster; working full-time or part-time in a clinical role as either registered nurses or doctors who care for children with bronchiolitis in New Zealand or Australian EDs or paediatric inpatient areas. The original PREDICT Bronchiolitis KT Study clinical leads will be included in the sample, where possible [4]. Bank or agency staff (nurses); interns/students, locums (medical); and clinicians not currently engaged in clinical practice will be excluded.

#### Outcome measures for qualitative study

Factors that contributed to sustainability/non-sustainability of improvements (i.e., no use of the five low-value practices) at intervention group hospitals 4 years post-trial completion including the sustainment of PREDICT Bronchiolitis KT Study implementation strategy;Factors that contributed to improvements (i.e. no use of the five low-value practices) or deterioration at control group hospitals 4 years post-trial completion, including the use of PREDICT Bronchiolitis KT Study implementation strategy;Fidelity to and adaptation of the PREDICT Bronchiolitis KT Study implementation strategy at intervention and control group hospitals 4 years following intervention delivery (2018, 2019, 2020, 2021) [4, 34].

### Data collection procedure

#### Clinician interviews

Eligible ED and paediatric inpatient area staff will contact the research staff directly, by email or phone, so a convenient date, time and location for the individual or group semi-structured interview can be arranged. Participants will be interviewed face-to-face or by video link (e.g., ZOOM), depending on the participants’ preferences and convenience. Consent will be implied if an eligible interested individual presents at the agreed upon time to participate in the semi-structured interview. The interviews will be conducted for approximately 30-45 minutes and will be digitally recorded using a voice recorder or via zoom (all recordings will be saved electronically to the Murdoch Children’s Research Institute secure platform). Verbal confirmation will be obtained for consent to audio-tape the interview.

#### Interview schedule and conduct

The interview schedule has been developed by the research team, which includes emergency physicians, nurses and researchers. The schedule includes open-ended questions to elicit participant’s views on how the PREDICT Bronchiolitis KT Study was perceived by staff; use and adaption of intervention materials; and potential barriers and enablers to sustaining practice change. The interview schedule will be piloted to ensure face and content validity.

#### Sample size

A maximum of three to five individuals per site (*n* = 78 to 130) from a cross section of nursing and medical staff from both ED and paediatric inpatient areas will be invited to participate in the interviews.

### Data analysis

Thematic analysis will be performed on qualitative transcribed interview data imported into NVIVO10 (QSR International Pty Ltd., Australia), using an iterative process and open coding relating extracts of text to key questions using saliency analysis i.e., the extent to which each code occurs, and implied importance (regularly mentioned or considered important by researchers or participants) [35]. Hospitals will be compared and contrasted by intervention and control group allocation from the PREDICT Bronchiolitis KT Study. Text will be cross indexed when it is relevant to more than one theme. Codes will be collapsed and decreased as analysis progresses. Cross-checking of the coding framework and discrepancies will be conducted by a second researcher and discussed to reach consensus. Participant quotes will be linked to the final agreed set of themes and sub-themes. When no new insights or issues between participant groups or between hospitals are reported over three consecutive interviews, data will be deemed saturated [36]. Themes will then be mapped to a sustainability framework(s) [23, 29, 37].

## Discussion

This study aims to evaluate if targeted, theory-informed interventions sustain improvements in bronchiolitis care (i.e. no use of the five low-value practices: salbutamol, glucocorticoids, antibiotics, adrenaline and CXRs) in the acute care period (first 24 hours of hospital presentation) in EDs and paediatric inpatient units, two-years (2019) after their implementation [34]. Results will help to inform the content and format/methods by which to deliver implementation strategies to promote and sustain evidence-based management in acute care ED and paediatric inpatient areas.

Within the field of implementation science, de-implementation is an emerging field of research, only appearing in the literature within the last decade [38, 39]. There are very few studies that have examined sustainability of successful implementation interventions, with even less examining sustainability of de-implementing low-value care following completion of a successful behaviour change trial [20]. The majority of sustainability studies have been conducted in community and public health settings and not in acute care settings [29]. Few studies provide an a priori definition of sustainability [20] and often use established implementation frameworks to examine sustainability instead of using a sustainability framework [29]. Whilst evaluating sustainability frameworks is an agreed research priority, there is no consensus within the literature on which sustainability framework is the most suitable to inform sustainable evidence-based practice changes in acute care settings. This could be attributed to the dynamic nature of sustainability and the nature of acute care areas and is likely to evolve over the coming years [29–31].

This study is novel and innovative as it examines the sustainability of a successful de-implementation intervention in the acute care setting, two- years following removal of the study supports. We will report sustainability of clinician behaviour changes and sustainment of evidence-based interventions to de-implement low-value care. Whilst there is no consensus on when implementation phases end and when the sustainability period commences [19, 20, 30], two- years was deemed an appropriate timeframe to assess sustainability in an ED and acute inpatient setting. We have an ‘a priori*’* definition of sustainability and are using an established sustainability framework which has been deemed as relevant and useful when exploring sustainability in acute care settings [23, 29]. As such, our study will contribute to our understanding of sustainability of de-implementing low-value practices in paediatric acute care settings, and advancing the science of sustainability research.

## Data Availability

Not applicable.

## Abbreviations

ACU: Australian Catholic University
CXR: Chest X-ray
ED: Emergency Department
GLM: Generalised Linear Mixed
HREC: Human Research Ethics Committee
ICU: Intensive Care Unit
KT: Knowledge Translation
MCRI: Murdoch Children’s Research Institute
NHMRC: National Health and Medical Research Council
PI: Principal Investigator
PREDICT: Paediatric Research in Emergency Departments International Collaborative Knowledge Translation
REDCap: Research Electronic Data Capture
